### Care as usual

Care as usual in the clinical setting involves standard psychosocial care provided by the oncological nurse during regular appointments. In most cases, this means that the patient’s perceptions after treatment and possible treatment-related problems or complications are discussed. However, RTW, work-related problems or treatment-induced work problems are not routinely discussed in this form of psychosocial care.

### Sample size

The calculation of the sample size is based on two earlier studies, because no recent data are available on the RTW of GI cancer patients from clinical patient cohorts. Data from 2005 on 220 GI cancer patients, provided by a large occupational health service in the Netherlands, show that two years after diagnosis, 63 % of patients had returned to work full-time [27]. Based on these data, it is hypothesized that the percentage of 63 % RTW in GI cancer patients is the maximum result of ‘care as usual’. In a study by Nieuwenhuijsen [28], an intervention group of 35 radiotherapy patients received a supportive work-related intervention in a hospital. RTW was measured between the end of curative treatment and the first day of (partial) work resumption. This was found to be 89 % after twelve months. The median time between enrolment and the end of treatment was 42 days. Earlier studies at the AMC show that the percentage of patients that RTW in the first 42 days is around 8 % [29, 30]. The RTW for the intervention group was therefore set at 89 %–8 % = 81 %.

The sample size is calculated using the Power and Sample Size Calculation program nQuery Advisor 7.0. A power of 80 % and a p value of <0.05 indicated that we should include a total of 216 patients, with a follow-up of twelve months, to indicate a difference of 81 % (intervention) versus 63 % RTW (care as usual). Allowing for a 20 % loss to follow-up and a 10 % one-year mortality rate, 309 patients should be included.

### Outcome measures and prognostic factors

Data on the primary and secondary outcomes, as well as prognostic factors such socio-demographic factors (i.e. age, gender, level of education), disease-related factors and work-related factors, will be gathered using five questionnaires: baseline (T0) and three (T1), six (T2), nine (T3) and twelve (T4) months after baseline. It will take approximately 30 min to complete a questionnaire. The primary outcome measure is RTW, defined as the time to a partial or full RTW, and measured as the number of calendar days between the first day of sick leave and the first day at work. The patient must have returned to work (part-time or full-time) for at least four successive weeks (independent of the number of contract hours). The secondary outcome parameters are work ability, work limitations, quality of life, RTW (yes/no) and direct/indirect costs.

#### Effect evaluation

The effectiveness of the study will be determined on the basis of the primary outcome RTW and the secondary outcomes work ability, work limitations and quality of life, assessed at a long-term follow-up at twelve months. RTW will be based on the patients’ self-reporting in the questionnaires (T0-T4).

Work ability will be assessed with reference to the first three questions of the Work Ability Index (WAI) [31], using a ten-point scale. These questions concern an evaluation of a patient’s current work ability compared to their lifetime best ability, and their current physical and mental work ability with respect to their job demands. Higher scores indicate a higher level of work ability (0 means not currently able to work at all, and 10 means work ability at its best). The index has been assessed as having good levels of reliability and validity [32].

Work limitations will be measured with the Work Limitation Questionnaire (WLQ) [33], using a five-point scale. This questionnaire evaluates work disability and productivity (loss) in people with health problems. It consists of four sub-scales with 25 items: work scheduling, physical demands, mental/social demands and output demands. The scale ranges from 0 to 100, with higher scores indicating more work limitations over the previous two weeks (0 means never limited and 100 means limited all of the time). The English version of the WLQ has been shown to be valid and reliable when used for cancer survivors [34]. The WLQ questionnaire has been translated into Dutch and is valid and reproducible at group level among cancer survivors [35].

Quality of life will be measured with two questionnaires; 1) the SF12 [36, 37], to compare the study participants with the normal population, and 2) the EORTC QLQ-C30 [38], to compare the quality of life of the study participants diagnosed with GI cancer with that of patients with other cancer diagnoses. These questionnaires provide insight in the participants’ feelings about their health and their ability to carry out their usual activities.

The SF12 consists of twelve items, providing scales for physical and mental health. Questions refer to the patient’s functional status, including their physical and social functioning and physical and emotional constraints and their general view of their own health. The physical and mental health scores are calculated using the scores of twelve questions. The questionnaire has a range from 0 to 100 (0 means the lowest level of health measured by the scales, and 100 indicates the highest level of health).

The EORTC QLQ-C30 contains 30 items, including five functional scales, three symptom scales, a global health status/Quality of Life scale and six single items. Scores range from 0 to 100. A higher score represents a higher (better) level of functioning or a higher (worse) level of symptoms.

#### Process evaluation

The process of the intervention will be evaluated with the following parameters: number of consultations within the intervention, number of consultations with other work-related support interventions, and participant satisfaction, measured with the self-reporting questionnaires. Participants may use any co-interventions that they wish to use; there will be no restrictions. In order to evaluate this, participants in both the intervention and the control groups will be asked in the self-reporting questionnaires about the type and number of co-interventions they received.

The content of the consultation, the number of referrals to the other types of support within the intervention, the evaluation (using the decision diagram) of whether the work-related support is sufficient and the health professionals’ general perceptions of and satisfaction with the intervention are measured using the protocol forms, which are completed during the meeting with the patient.

#### Economic evaluation

A cost-effectiveness analysis (CEA) will be performed, taking a societal perspective. The economic evaluation will cover work-related costs to society and the cost of healthcare for the patients themselves and for their employers. The following costs (payment discipline for intervention meetings/nurse training/days of patient’s hospital admission/patients’ income and work adjustments) will be measured for the intervention group as well as for the control group.

Indirect costs, including absenteeism (determined as the total number of days of sick leave from the first day of sick leave at baseline until follow-up), lost earnings (determined as the difference in income between baseline and follow-up) and work productivity (measured using the Work Limitation Questionnaire), will be taken into account and obtained with the patients’ questionnaires (T0-T4). Direct costs such as the duration of the intervention (in minutes) for each patient by the healthcare professional will be presented. The healthcare professionals will record the duration of each meeting.

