#### Economic evaluation

The direct and indirect costs will be calculated for each participant. Using bootstrapping, mean differences in direct, indirect, and total costs will be calculated between the control group and the intervention group [43]. Incremental cost-effectiveness ratios will be calculated by assessing the ratio of the differences in costs between the intervention and control groups to the differences in RTW rates between the groups.

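### The societal cost total lists both absenteeism and lost earnings with no rule against overlap, so pay lost through absence is liable to be counted twice

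*Protocol article*

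**What the plan says.** Two sections of the Protocol article headed Economic evaluation bear on this point.

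The one under Outcome measures sets the viewpoint: "A cost-effectiveness analysis (CEA) will be performed, taking a societal perspective". Patients' income is among the costs to be measured in both arms. Three items are then given as indirect costs. The first two stand next to each other in one list: "absenteeism (determined as the total number of days of sick leave from the first day of sick leave at baseline until follow-up), lost earnings". The earnings item is taken as the change in a patient's income since baseline. The third item is productivity at work, from the Work Limitation Questionnaire.

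The one under Statistical analysis calculates direct and indirect costs for each participant. By bootstrapping, "mean differences in direct, indirect, and total costs will be calculated". The incremental ratio is "the ratio of the differences in costs between the intervention and control groups to the differences in RTW rates between the groups".

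Neither section says how a day of absence is priced, or how absence and lost earnings are kept apart once both are in the indirect costs.

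**The concern.** A societal total should contain each unit of lost work once. When a patient is off sick, society loses the production of that day. Who bears the loss (patient, employer or insurer) is a matter of distribution. The patient's fall in income because of that absence is therefore part of a loss already counted, or a transfer between parties. Adding it to the value of the absent days counts it again.

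The error has a direction. It enlarges the cost of absence in proportion, so it enlarges the apparent saving of whichever arm has fewer sick days. The intervention is meant to shorten absence, so if it works the overlap favours it. Cost-effectiveness is the declared aim of the study in the Background, Objective and Discussion, so the cost difference is a headline result.

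A smaller matter is the start of the absence count. Patients must be on sick leave to enter and are randomised only after the baseline questionnaire is received. Counting from the first day of sick leave therefore takes in days that the intervention cannot affect.

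**Working it through.** **Is there a figure to reproduce?** The article gives no unit cost, income-replacement rate or cost result. Its sample-size figures do not bear on this point, except that the 63% and 81% return-to-work rates serve below as an illustration.

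**Step 1: overlap factor.** Let v be the production value of one absent day, with pay taken as equal to v, and let L be the share of pay that the patient loses on that day. L is an assumption.

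- Absence item per day: v.
- Lost-earnings item for the same day: L × v.
- Sum: v + Lv = v(1+L), where the societal loss is v.

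| L (assumed) | Factor 1+L |
|---|---|
| 0 (full pay continues) | 1.0 |
| 0.1 | 1.1 |
| 0.3 | 1.3 |
| 0.5 | 1.5 |
| 1.0 (no pay continues) | 2.0 |

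The study population includes self-employed patients, for whom continued pay cannot be taken for granted, so L is unlikely to be zero throughout.

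**Step 2: what this does to a cost difference.** As an illustration, take exponential return-to-work times that reach 63% and 81% at 365 days. The mean number of absent days up to 365 is p × 365 / (−ln(1−p)).

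- Usual care: 0.63 × 365 / 0.994 = 231 days.
- Intervention: 0.81 × 365 / 1.661 = 178 days.
- Difference: about 53 days.

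With the overlap, these 53 days are charged as 53 × 1.1 = 58 days at L = 0.1 and 53 × 1.3 = 69 days at L = 0.3. The excess is L × v × 53 per patient. It assumes the same L in both arms and that the earnings item captures all pay lost on the absent days.

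**Step 3: days before randomisation.** These precede allocation, so they have the same expectation in both arms and cancel in the difference. A simulation with 155 patients per arm, the return-to-work model above and exponential prior sick leave of assumed mean length gave:

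| Assumed mean prior sick leave | Mean difference in days, without / with prior days | Standard error, without / with prior days |
|---|---|---|
| 14 days | −53.1 / −53.1 | 14.6 / 14.7 |
| 30 days | −53.4 / −53.4 | 14.4 / 14.8 |
| 60 days | −53.4 / −53.3 | 14.9 / 16.3 |

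There is no bias, and the standard error rises by roughly 1% to 10%. The article's phrase on the starting day is also ambiguous, and the earnings item runs from baseline, so the two items may cover different periods.

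**The case against.** The best defence is that the article only says the three items will be taken into account. It measures absenteeism in days, sets no price, and never says that each item is turned into money at full value and added. Valuation is the kind of detail a condensed article leaves to a fuller document. This is a fair limit on how much can be claimed, but it does not remove the point. The choice of items and the societal viewpoint are stated, both items are called indirect costs, and the only destination the article gives for indirect costs is the per-participant and total costs.

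A second objection is that the factor 1+L presumes a comparison with income before illness. Lost earnings is defined as a change from baseline, and patients are already on sick leave then. If baseline income is already sick pay, the change need not reflect the shortfall on absent days, and the overlap could be nil. Income can also change through job loss or fewer hours, and the overlap is nil where full pay continues. All of this stands: 1+L describes full overlap and is not a prediction.

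A reader might go further and infer that the ratio uses total costs only, so that earlier return to work is credited in both numerator and denominator. The text does not support this. It speaks of cost differences, plans direct, indirect and total differences, and refers to ratios in the plural. Nor does the article's silence on joint uncertainty for the ratio show that none will be given, since this is commonly left to the full protocol or analysis plan.

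**Conclusion.** The point holds as a risk of double counting built into the listed cost items. Read as written, under "taking a societal perspective" the indirect and total costs contain both absence and the income lost because of it, and savings in the arm with fewer sick days tend to be overstated. Under full overlap the absence cost is 10% too high at L = 0.1 and 30% too high at L = 0.3. This rests on an assumed L and on valuing absence at full production, neither of which the article gives.

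A reader might infer that the cost-effectiveness aim will be answered wrongly. That is too strong, because the size and even the presence of the error depend on a valuation that is not stated. It would also be wrong to infer that sick days before randomisation bias the comparison: they add noise only. The primary outcome, its test and the sample size are not affected. The economic plan should be corrected because its result is the declared aim and the correction is cheap.

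**What to change.** State in the economic analysis that the societal total counts lost work once: days of absence under one named valuation, plus productivity loss while at work, each entered a single time. Take lost earnings out of that total and report it in a separate table from the patient's perspective, where it is informative in its own right.

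As a minor gain in precision, count absence days from randomisation to 12 months in both arms, which also settles the ambiguous starting day.

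The cost is a change of wording and a small amount of programming. No new data are needed, because sick leave and income are already collected by questionnaire from baseline to twelve months. The downside is that the estimated savings may be smaller.

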#### Prognostic factors

The prognostic factors include age, gender, marital status (married/single/cohabiting/widowed/divorced), education (seven categories), diagnosis (primary GI cancer diagnosis: oesophagus, stomach, liver, pancreas, biliary, small intestine, colon or rectum), treatment type (surgery, radiotherapy, chemotherapy, hormonal therapy, other) and treatment duration assessed with the self-reporting questionnaires. Fatigue is measured using the Multidimensional Fatigue Inventory questionnaire (MFI) [39], with 20 items divided into five sub-scales: general fatigue, physical fatigue, reduced activity, reduced motivation and mental fatigue. The sub-scale scores range from 4 to 20; a higher (implies 20) score indicates greater fatigue. Depression is measured using the scale developed by the Centre for Epidemiologic Studies for Depression (CES-D) [40], scored with 20 items. The scores range from 0 to 60; a higher (implies 60) score indicates greater depressive symptoms weighted for the past week. Cognitive functioning is measured with the Cognitive Symptom Checklist-Work, Dutch Version (CSC-W DV), containing 19 items, with the sub-scales for working memory and executive function. Scores range from 0 to 100, with higher scores indicating more cognitive symptoms (i.e., more limitations) in the work context. This questionnaire has been translated and a customized version of the Cognitive Symptom Checklist-Work (CSC-W) [41] validation article will be published.

#### Descriptive factors

The descriptive factors include breadwinner status (yes/no), job position (permanent contract/temporary contract/temporary worker/self-employed/other), employment status (employed/unemployed/self-employed/pension), years in current position, and company size (large 100 ≥ employees/medium-sized 10–100 employees/small 1–10 employees, or not applicable; self-employed), which will be assessed with the self-reporting questionnaires. The stage of cancer will be assessed from the patient’s medical records. Furthermore, the Perception and Judgement of Work (VBBA) [42] questionnaire will be used, with the sub-scale ‘physical workload’ containing seven items. The scores range from 0 to 21; a higher score indicates a higher physical workload. The importance of work is measured with a Visual Analogue Scale (VAS-scale), with a line running from 0 (not important) to 10 (most important).

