### Randomization

When the researcher has received the baseline questionnaire, the patient will be randomized to 1) the intervention group that will receive tailored work-related support, or 2) the control group that will receive care as usual. A computerized randomization programme ALEA [24] will be used to do this. As patients differ between the participating hospitals in terms of diagnosis, demographic factors and age, and because these factors are important prognostic factors for RTW [25], randomization will be stratified for gender, age (age groups: 18–54 and 55–63 years) and hospital, so as to prevent bias due to unequal randomization. Minimization will be applied to equalize group sizes. The patients, healthcare professionals and researchers will not be blinded for the group assignment.

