### The intervention: tailored work-related support

The intervention consists of three individual meetings between a patient and a healthcare professional within the clinical setting. As work-related problems differ in severity, the intervention will be divided into three types of support, namely: support A, support B and support C.

In an earlier study (published separately) with an expert panel consisting of physicians, oncological nurses, (oncological) occupational physicians, social workers and patients, a decision diagram was drawn up that, based on a list of factors from the literature, refers the patient to one of the three types of support (A, B or C) for the tailored work-related support intervention (see Table 1). These factors have been added to the patients’ baseline questionnaire (T0). Based on a participant’s answers to this baseline questionnaire and the decision diagram, the researcher will refer the participant to the tailored types of support A, B or C.

**Table 1 Tab1:** Overview of tailored support (A, B and C), depending on type of work-related problems experienced

Healthcare professional	A (oncological nurse)	B (occupational physician)	C (multidisciplinary team)
Factors (differ according to type of support)	• Fatigue • Pain • Treatment • Uncertainty about the future • Lack of support from family and friends	• Lack of support in work environment • Neuropsychological symptoms • Occurrence of side effects that prevent patient from doing current work *Combination of the following factors:* Number of working hours—treatment—stage of cancer and fatigue	*Combination of the following factors:* Medical complications—fatigue—stage of cancer—type of cancer—perception of change regarding work—dietary problems

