#### Primary study parameter

For the primary outcome measure (RTW), the number of days until RTW (either full or partial) will be analysed using a Kaplan-Meier survival method. The patients who dropped out of the study will be censored. The differences between the intervention and the control group will be tested using a log rank test. If significant differences between the intervention and control groups are found with regard to the prognostic variables, the outcome variable RTW will be adjusted for these variables in a multivariate Cox regression analysis. In addition to the ITT analysis aimed at ‘all—cause return to work’, the analysis will be performed excluding those patients who died during follow-up and those who have a life expectancy of less than a few months, because they will not RTW.

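### Cancer stage is collected but has no route into the adjusted Cox model for return to work; pre-specify it as a covariate instead of leaving it descriptive

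*Protocol article*

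**What the plan says.** The article divides baseline variables into two named classes.

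- **Prognostic factors.** The section opens "The prognostic factors include age, gender, marital status" and goes on to education, tumour site, treatment type and duration, fatigue, depression and cognitive functioning. Stage is not listed.
- **Descriptive factors.** Stage is here: "The stage of cancer will be assessed from the patient’s medical records".

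Only the first class is tied to the model. Under Primary study parameter the condition is "If significant differences between the intervention and control groups are found with regard to the prognostic variables", and then "the outcome variable RTW will be adjusted for these variables in a multivariate Cox regression analysis". The Statistical analysis section sets the threshold for significance at 0.05.

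Two other places bear on stage. The expert-panel decision diagram, "based on a list of factors from the literature, refers the patient to one of the three types of support", has stage in one combination for support B ("Number of working hours—treatment—stage of cancer and fatigue") and in one for support C ("Medical complications—fatigue—stage of cancer—type of cancer—perception of change regarding work—dietary problems"). Under Randomization, "randomization will be stratified for gender, age (age groups: 18–54 and 55–63 years) and hospital"; stage is not among these factors.

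**The concern.** The class that a variable is put in decides whether it can be adjusted for. A descriptive variable has no route into the Cox model, even with a large imbalance. Stage is a baseline measure of disease severity, its balance is left to chance, and the trial's own referral tool uses it. Tumour site, treatment and fatigue also appear in that tool, and all three are on the prognostic list. The article gives no reason for treating stage differently.

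At stake are the precision of the treatment estimate and how it would be read if the arms happened to differ in stage. Adjustment added after such a difference is seen would be post hoc and open to dispute.

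**Working it through.** **1. The plan's own figures.** For 81% v 63%, two-sided 5%, 80% power, the two-proportion formula with continuity correction gives 108 per arm, 216 in total (97 per arm without the correction). Then 216 / (1 − 0.20 − 0.10) = 308.6, so 309. Both stated figures reproduce, and neither depends on how stage is classed.

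**2. Route into the model.** A covariate must (a) be on the prognostic list and (b) have p ≤ 0.05 at baseline. Stage fails (a), so (b) is never reached.

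**3. What relabelling alone would do.** Under randomization (b) is met by chance in about 5% of trials. Take 55% v 45% advanced stage, an assumed split:

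- 108 per arm: SE = √(0.5 × 0.5 × 2/108) = 0.068; z = 0.10/0.068 = 1.47; p = 0.14.
- 155 per arm (all 310): SE = 0.057; z = 1.76; p = 0.08.

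Neither triggers adjustment. If stage has a hazard ratio (HR) of 0.5 for RTW, this imbalance shifts the treatment HR by a factor of about exp(0.10 × ln 2) = 1.07. At 108 per arm the split would have to reach about 1.96 × 0.068 = 13 points to trigger. In 2,000 simulated trials per setting, applying the test rule to stage moved power only from 87.5% to 87.6% (stage HR 0.5) and from 79.7% to 80.6% (0.35).

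**4. What pre-specifying stage would do.** From the article: n = 216 and one-year RTW of 63% v 81%. With exponential times the treatment HR is ln(1 − 0.81)/ln(1 − 0.63) = 1.67. Expected events are 108 × 0.81 + 108 × 0.63 = 156. Assumed, because the article gives no figure: a two-level stage, the share at the higher stage, and its HR for RTW. Death and dropout are not modelled. Power of the Cox treatment test without v with stage:

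| Stage HR | 40% higher stage | 50% higher stage |
|---|---|---|
| 1.0 | 88.0 v 87.8 | – |
| 0.85 | – | 88.6 v 89.0 |
| 0.7 | 89.2 v 90.0 | 88.0 v 89.4 |
| 0.5 | 85.0 v 88.2 | 85.6 v 89.1 |
| 0.35 | 77.2 v 85.8 | 78.6 v 88.6 |

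The 40% column has 600 trials per setting, so each entry has a Monte Carlo error of about 1.5 points (√(0.85 × 0.15/600)). Further runs at a 50% share gave 84 v 89 and 87.5 v 89.8 at stage HR 0.5, and 77 v 87 and 79.7 v 88.8 at 0.35. The gain is therefore about 0 to 1 points at 0.7 or weaker, about 2 to 5 at 0.5, and about 9 to 10 at 0.35.

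**5. Estimate and error rate.** At stage HRs of 0.7, 0.5 and 0.35 (40% share) the unadjusted treatment HR averaged 1.65, 1.62 and 1.56; the adjusted one stayed at 1.66 to 1.67. With no treatment effect, the rejection rate was about 3% to 6% with or without stage.

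**The case against.** Several points on the other side stand.

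- **The primary test is unaffected.** The planned comparison is an unadjusted log rank test, which is valid under randomization. A reader might infer that the primary result is biased. It is not: the error rate already allows for chance imbalance, and the lower unadjusted HR is an average over stage groups, not confounding.
- **The label by itself does little.** A reader might infer that moving stage to the other list cures the problem. Step 3 shows that it does not, because the baseline-test trigger does most of the blocking. That trigger affects every listed prognostic factor in the same way.
- **Table 1 is not a prognostic list.** A reader might infer that the article contradicts itself. But the diagram uses stage only in combination with other factors, to choose a type of support, and never says that stage predicts time to RTW. Working hours and dietary problems are also in the diagram and absent from the prognostic list.
- **A strong stage effect is not established.** Enrolment is restricted to curative intent, which plausibly narrows the stage range. Tumour site and treatment type may carry part of the same information, whereas the simulations give stage full credit as the only covariate.
- **Data quality is not stated.** The article names medical records as the source. It does not say that stage will be complete.

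One point carries less weight. The prognostic section uses an open verb, and the outcome section mentions disease-related factors, so stage might be counted in. But the article places it explicitly under the other heading, and that outweighs the general wording.

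**Conclusion.** The point holds as a matter of efficiency and robustness, not validity. As the article stands, stage cannot enter the adjusted model, and no reason is given. The cost is negligible if stage is weakly related to RTW (hazard ratio 0.7 or nearer 1), modest at 0.5, and material only for an effect as strong as 0.35. Even there, unadjusted power is about 77% to 80%, close to the planned 80%. These figures rest on 216 evaluable patients, exponential times, a two-level stage with 40% or 50% at the higher level, and stage as the only covariate. None of the stage inputs is in the documents. The change is worth making because it costs so little, not because a large loss has been shown.

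**What to change.** Under Primary study parameter, name baseline stage as a covariate in the Cox model for RTW, to be included whatever any baseline significance test shows. Define it as the stage known at randomization, in a simple grouping comparable across the enrolled tumour sites (for example early v locally advanced), and fix that grouping before any unblinded analysis. Moving stage to the prognostic list is tidy but not sufficient while the test trigger remains.

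The cost is one or two degrees of freedom against about 150 events, plus the work of defining the grouping. Stage is already to be taken from records, and the sample size of 216, inflated to 309, does not change. The log rank test can stay as the primary test; the gain in precision then applies to the adjusted estimate.
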